### Safety

2.9

This trial will be conducted in accordance with the Declaration of Helsinki and established clinical research guidelines. Prior to enrollment, all participants will provide written informed consent after being fully informed of the potential risks and benefits of participation. Baseline health assessments will be performed by qualified physicians to confirm eligibility and ensure participants’ suitability for exercise testing and interventions. Throughout the intervention period, participants’ health status will be closely monitored, with systematic documentation of any safety-related information, including modifications to the exercise regimen, participant-reported symptoms, and monitoring results. Additionally, the trial will be immediately discontinued for any participant presenting with: (a) SBP > 180 mmHg or DBP > 110 mmHg; (b) exercise-induced angina or dyspnea; (c) syncope or dizziness; or (d) severe musculoskeletal injury. Any affected participant will receive appropriate medical treatment. Emergency medical support will be available on site during all exercise sessions.

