### Assessments and procedures

2.4

All study outcomes and corresponding assessment time points are presented in **Table 2**. The primary outcome is the change in HFC, as measured by magnetic resonance imaging, from baseline to 12 weeks post-intervention. Secondary outcomes encompassed: (1) anthropometric parameters; (2) body composition and abdominal fat; (3) cardiorespiratory fitness; (4) cardiometabolic biomarkers; and (5) Indicators of liver inflammation and fibrosis. Detailed measurement procedures are described below.

**Table 2 T2:** The study schedule.

Study phase	Screening	0 week	4 week	8 week	12 week
Informed consent	✓	–	–	–	–
Demographics	✓	–	–	–	–
Medical history	✓	–	–	–	–
Lifestyle counseling	✓	✓	✓	✓	✓
Medications report	✓	✓	✓	✓	✓
Physical and diet assessment	✓	✓	✓	✓	✓
Anthropometric assessment	✓	✓	✓	✓	✓
Randomization	✓	–	–	–	–
MRI-PDFF	–	✓	–	–	✓
Cardiometabolic biomarkers	✓	✓	–	–	✓
Liver inflammatory biomarkers	✓	–	–	–	✓
Body composition	✓	✓	–	–	✓
Cardiorespiratory fitness	✓	✓	–	–	✓
Quality of life	✓	✓	–	–	✓
Adherence	✓	✓	✓	✓	✓
AEs	✓	✓	✓	✓	✓

MRI-PDFF, Magnetic Resonance Imaging - Proton Density Fat Fraction; AEs, adverse events.

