### Intervention

2.5

The intervention period will last for 12 weeks, with 3 supervised training sessions per week at the community fitness center. Each session will consist of a warm-up (5–10 minutes), a main exercise phase (30–60 minutes) on a treadmill, and a cool-down (3–5 minutes). To maximize training adaptations while ensuring safety, we have designed a progressive intensity protocol. Specifically, the MICT group will exercise at 45–55% of Heart Rate Reserve (HRR). The HIIT and LHIIT groups will perform high-intensity intervals (4-minute work intervals at 70–90% HRR separated by 3-minute active recovery intervals at 40% HRR) and the training load will be adjusted monthly in accordance with the CPET. The detailed progression of intensity and heart rate targets is presented in **Figure 2**.

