### Sample size

2.6

The sample size is calculated based on the primary comparison between the HIIT and MICT groups regarding the absolute change in MRI-PDFF from baseline to 12 weeks. Based on the previous study that implemented a similar intervention duration, we anticipated an absolute reduction in hepatic fat content of -1.7% (SD 1.1%) for the HIIT group and -0.9% (SD 0.7%) for the MICT group (22). Assuming a pooled standard deviation of 0.92% and a two-sided significance level of 0.05, a sample size of 28 participants per group is required to achieve 90% statistical power to detect the between-group difference. To account for a potential dropout rate of 20%, the sample size is adjusted to 35 participants per group. Consequently, a total of 105 participants will be recruited, with equal allocation (1:1:1) to the HIIT, MICT, and LHIIT groups.

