### Statistical analysis plan

2.7

Baseline characteristics and study outcomes will be summarized using descriptive statistics. The normality of continuous variables will be assessed using the Shapiro-Wilk test and visual inspection of histograms and Q-Q plots. Continuous variables with a normal distribution will be presented as means ± standard deviations (SD), while non-normally distributed variables will be reported as medians and interquartile ranges (IQR). Treatment effects will be reported as the estimated mean difference (MD) between groups with 95% confidence intervals (CIs) to provide a clear estimation of the effect size. Categorical variables will be expressed as frequencies and percentages (n, %). Baseline differences between groups will be assessed using one-way ANOVA or Kruskal-Wallis tests for continuous variables, and Chi-square tests or Fisher’s exact tests for categorical variables.

The analysis will be conducted according to the Intention-to-Treat (ITT) principle, including all randomized participants (N = 105) for both primary and secondary endpoints. To address missing data arising from participant withdrawal, Multiple Imputation by Chained Equations (MICE) (m=20 imputed datasets) will be performed prior to the primary analysis. Treatment effects will be evaluated using analysis of covariance (ANCOVA). The post-intervention measurements will be included as the dependent variable. Fixed effects will include group (HIIT, MICT, LHIIT), and the baseline measurements will be included as a covariate. The results from the imputed datasets will be pooled using Rubin’s rules. Tukey’s Honestly Significant Difference test will be used for *post-hoc* pairwise comparisons. Furthermore, sensitivity analyses for primary outcome will be conducted to assess the robustness of the results. These will include: (1) a Per-Protocol analysis; (2) an analysis excluding participants with >5% body weight change; and (3) an analysis including percentage body weight change as a covariate in the primary ANCOVA model. All statistical analyses will be performed using R software (version 4.5.1). A two-sided p-value< 0.05 will be considered statistically significant.

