### Compliance and adherence

2.8

At enrollment, all participants will receive standardized education to ensure full understanding of the intervention requirements and the importance of adherence. Exercise sessions will be delivered under direct supervision by certified exercise trainers, with adherence monitored through detailed attendance records and continuous heart rate tracking. To enhance participant adherence and motivation, participants will receive personalized feedback on their progress from the researchers, and will be contacted via text message or phone calls if they miss more than one session. Furthermore, to maintain consistency in habitual dietary intake, participants will be required to complete a 3-day dietary record (two weekdays and one weekend day) using a mobile application every two weeks. These logs, including food logs and meal photographs, will be reviewed by a study dietitian, who will provide immediate feedback if average daily energy intake deviates by more than $10\%$ from the established baseline level.

Adherence will be quantified as the proportion of prescribed sessions attended and completed within the target training intensity zone. The minimum adherence threshold for inclusion in the per-protocol analysis is set at 70%. Participants whose adherence falls below this level will receive additional counseling and behavioral support from the research team. If adherence remains inadequate despite these measures, withdrawal from the trial may be considered. All cases of withdrawal and their reasons will be documented and transparently reported in the final trial outcomes.

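### Section 2.9 does not say whether a safety event stops the exercise or ends trial participation; read literally, it can turn an obtainable week-12 MRI-PDFF into an imputed value

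*Protocol article*

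**What the plan says.** Section 2.9 lists four groups of events: blood pressure above 180 systolic or 110 diastolic, then "b) exercise-induced angina or dyspnea; (c) syncope or dizziness", and severe musculoskeletal injury. For these, "the trial will be immediately discontinued for any participant presenting with" them. The only consequence stated afterwards is medical treatment.

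The related provisions are:

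- **Outcome timing (2.4).** The primary outcome is the change in hepatic fat content "as measured by magnetic resonance imaging, from baseline to 12 weeks post-intervention". Table 2 schedules MRI-PDFF at weeks 0 and 12 only.
- **Analysis (2.7).** The analysis is intention-to-treat, "including all randomized participants (N = 105) for both primary and secondary endpoints". Missing values are handled as follows: "To address missing data arising from participant withdrawal, Multiple Imputation by Chained Equations (MICE", with 20 imputed datasets).
- **Adherence (2.8).** For persistently poor adherence, "withdrawal from the trial may be considered".
- **Intensity (2.5).** In the comparator, "the MICT group will exercise at 45–55% of Heart Rate Reserve (HRR"); the HIIT and LHIIT work intervals run at 70–90%.
- **Dropout (2.6).** "To account for a potential dropout rate of 20%, the sample size is adjusted to 35 participants per group".

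**The concern.** Stopping the exercise and ending participation are different decisions. The first protects the participant. The second also removes the outcome measurement. An intention-to-treat comparison needs the week-12 value of everyone randomised, including those who had to stop training, and most of the listed events would not prevent an MRI some weeks later.

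If site staff follow the sentence literally, a participant stopped between baseline and week 12 has no post-baseline value of the primary outcome. The value is then missing for a reason tied to symptoms during exertion, and such events may be more frequent at 70–90% than at 45–55% of heart rate reserve. Imputation would rest mainly on people who did not have such an event, and no hepatic fat value observed after a 2.9 stop would exist to check it. None of the three sensitivity analyses listed in 2.7 bears on this. The triggers themselves are not in question.

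**Working it through.** **Step 1. Reproduce the plan's own figures (2.6).** The inputs are changes of −1.7 (SD 1.1) for HIIT and −0.9 (SD 0.7) for MICT, two-sided α 0.05 and power 90%.

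- Pooled SD = √((1.1² + 0.7²)/2) = 0.92, as stated.
- n per arm = 2 × (1.96 + 1.28)² × 0.92² / 0.80² ≈ 27.8, so 28, as stated.
- 28 / 0.8 = 35, as stated.
- Planned standard error of the contrast = 0.92 × √(2/28) = 0.246 percentage points.

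The dropout allowance covers lost precision. It does not cover bias from who is lost.

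**Step 2. Trace the literal reading.** A 2.9 event between week 0 and week 12 ends participation. Table 2 has no MRI between those visits, so no post-baseline PDFF exists. All 105 are analysed, so the value is imputed. The link from a 2.9 stop to the imputation step is an inference: 2.7 speaks of withdrawal, and 2.9 does not use that word.

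**Step 3. Illustrate the size.** The article gives no event rate, so everything in this step beyond the planning means and the 35 per arm is an assumption. Completers are taken to change by the planning means (contrast −0.80), and imputed values to centre on completers of the same arm. Let k be the number lost in an arm and d the amount by which their true reduction falls short of that arm's completers. Subscripts H and M stand for HIIT and MICT. Then

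shift = imputed contrast − all-randomised contrast = −(k_H·d_H − k_M·d_M)/35,

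where a negative shift means that the HIIT benefit is overstated.

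| Scenario | k = 1 | k = 3 | k = 7 (extreme) |
|---|---|---|---|
| (i) HIIT only, true change zero (d_H = 1.7) | −0.05 | −0.15 | −0.34 |
| (ii) MICT only, true change zero (d_M = 0.9) | +0.03 | +0.08 | +0.18 |
| (iii) HIIT only, 0.8 better than completers (d_H = −0.8) | +0.02 | +0.07 | +0.16 |
| (iv) k in each arm, true change zero in both | −0.02 | −0.07 | −0.16 |
| (v) k in each arm, same shortfall | 0 | 0 | 0 |

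Worked example, (i) with k = 3: −(3 × 1.7)/35 = −0.146.

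For 1 to 3 lost, the shift runs from 0.15 of overstatement to 0.08 of understatement. The column for 7 assigns the whole 20% allowance of an arm (0.20 × 35 = 7) to safety stops and is shown only as a bound. One entry, 0.34, exceeds the standard error of 0.246. If data from weeks 4 and 8 exist for these people and are used as predictors in the imputation, the shifts could be smaller.

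**The case against.** The strongest reply is that the sentence is loosely worded and means the exercise. The stop is immediate, most of the triggers are acute events, and the neighbouring text concerns treatment and emergency support at exercise sessions. Section 2.9 also lists changes to the exercise regimen among the safety information to be recorded, which suggests that some people continue on a modified regimen. Table 2 exempts nobody from the week-12 scan, and 2.7 counts everyone randomised. A fuller protocol, not shown, may settle the matter. All of this stands as a reason to call the wording ambiguous. It does not make the sentence safe to follow as written, and if the authors meant only exercise, the amendment simply says so.

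A reader might take the phrase in 2.8, "withdrawal from the trial may be considered", as proof that 2.9 also means the end of participation. It is not. The two sentences share only the words for the trial itself, and 2.8 describes a discretionary step after counselling for poor adherence.

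A reader might also infer that the HIIT benefit will be overstated. The documents do not support that. They give no event rate in any arm, the participants are supervised adults aged 18–45 without uncontrolled blood pressure or conditions that preclude exercise, and the sign of the shift changes with the scenario.

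Section 2.8 promises that withdrawals and their reasons will be reported, so an imbalance between arms would be visible. That would not recover a scan that was never done.

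**Conclusion.** The point holds as a minor one about ambiguous wording. Read literally, 2.9 can cost the trial an obtainable primary-outcome value for a symptom-related and possibly arm-dependent reason. It is not an established departure from intention-to-treat and not a demonstrated bias: the narrower meaning is plausible, and the size and direction of any effect are unknown. With 1 to 3 of 35 lost in one or both arms, the non-zero scenarios move the HIIT–MICT contrast by about 0.02 to 0.15 percentage points, up or down depending on who is lost, against a planned standard error of 0.25. These figures rest on assumed numbers of events, assumed true responses of those lost, and imputation centred on same-arm completers.

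**What to change.** Keep triggers (a) to (d) unchanged and replace the wording of the consequence with two sentences, for example: *Any of these events immediately stops the session, the test or the training, as clinically required, and does not end trial participation. The scheduled week-12 MRI-PDFF is still obtained unless the participant withdraws consent or scanning is unsafe.* Section 2.7 needs no change, since imputation then applies only where the scan could not be obtained.

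The cost is a short wording amendment. The week-12 scan is already scheduled for everyone, so no visits, participants or staff are added, and protection of participants is unaffected. The downside is that if people who stop training respond less, the measured contrast will be somewhat smaller. In scenario (iv) it is 0.80 × (1 − k/35), that is 0.78 or 0.73 for 1 or 3 lost per arm (0.64 in the extreme case of 7), instead of 0.80. That smaller value is the one an intention-to-treat analysis is meant to estimate. Scans that are skipped cannot be recovered later, so the change should be made before participants reach week 12.

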### Data management

2.10

Study data will first be documented on standardized paper case report forms and then independently entered into a secure electronic database by two trained research staff members to ensure accuracy. The database is protected with role-based access controls, allowing only authorized personnel to view or modify study data. Routine quality assurance procedures will be performed, including verification of consistency between original records and electronic entries, checks for data completeness and logical integrity, and identification of outliers or missing values. Any discrepancies will be promptly reviewed and resolved in consultation with the principal investigator. In compliance with regulatory requirements and the approval of the institutional ethics committee, all study-related materials, including raw data, processed datasets, analysis outputs, and biological samples, will be securely archived for a minimum of five years following study completion.

Regarding data sharing, in line with principles of transparency and reproducibility, de-identified study data may be made available to qualified researchers upon reasonable request. Access to the dataset will require prior approval from the principal investigator and agreement to use the data solely for scientific purposes consistent with the aims of the study. Requests for data access will be documented, and approved users will be required to comply with institutional and ethical guidelines for secondary data use.

An independent Data Monitoring Committee (DMC) will not be established for this trial. The study is a single-center, investigator-initiated clinical trial involving exercise interventions of moderate intensity, which are generally considered low to moderate risk. Given the relatively small sample size, the short intervention period (12 weeks), and the non-pharmacological nature of the intervention, the establishment of an independent DMC is not deemed necessary.

### Adverse events

2.11

All AEs will be documented in detail, including their type, timing, severity, management strategies, and clinical outcomes. Particular attention will be paid to exercise-related musculoskeletal injuries, cardiovascular incidents, and symptoms of overtraining. Investigators will receive pre-trial training to ensure standardized identification, documentation, and reporting of AEs.

SAEs, irrespective of their potential association with the study intervention, will be reported in accordance with regulatory requirements. Each SAE will be submitted in writing to the Ethics Committee within seven calendar days of occurrence or identification. Non-serious adverse events will also be documented and subjected to periodic review to ensure participant safety and data integrity. Safety data will be reviewed regularly by the study team and Ethics Committee.

## Discussion

3

MASLD is the most prevalent chronic liver disease worldwide (23), strongly linked to increased cardiometabolic risk and underscoring the critical role of exercise interventions in its management (9, 24). This study was specifically designed to examine the effect of exercise intensity on HFC in individuals with MASLD. By employing MRI-PDFF as a standardized and reproducible outcome measure and balancing energy consumption between groups, the study design enhances methodological rigor. The anticipated findings may provide clinically relevant insights that contribute to refining exercise prescriptions for MASLD, offering more precise recommendations regarding exercise intensity while aligning with current international guidelines.

This study is a three-arm parallel randomized controlled trial and, to the best of our knowledge, represents the first attempt to investigate the effects of exercise intensity on HFC reduction under both energy-matched and unmatched conditions. Previous studies attempting to isolate the effect of exercise intensity on HFC in patients with NAFLD have been limited by methodological constraints. For instance, Zhang et al. conducted a long-term intervention (12 months); however, the differences in total exercise volume, compounded by the reduction in intensity within the high-intensity group during the intervention, obscured the specific role of intensity (25). Similarly, Keating et al. investigated the impact of exercise dose on HFC reduction across multiple dimensions(frequency, intensity, and volume); however, the simultaneous manipulation of these variables introduced excessive confounding factors, precluding a clear delineation of the intensity-specific effects (26). To address the volume confounder, Winn et al. implemented an energy-matched design comparing HIIT and MICT. Although they reported a clinically relevant trend where HIIT reduced HFC by 84% more than MICT, the study was underpowered due to a small sample size and short duration (4 weeks), resulting in a lack of statistical significance (10). Filling the gap for lower-volume protocols, Sabag et al. found that 12 weeks of low-volume HIIT reduced HFC by 89% more than MICT, but no statistical difference was observed between groups (22). These findings suggest a potential superiority of higher intensity, but the evidence remains inconclusive. As highlighted in a meta-analysis by Sabag et al., there is a paucity of studies directly comparing HIIT and MICT, with Winn et al. being the only prior study to strictly match energy expenditure. Therefore, our study is critical to filling this void by rigorously investigating the independent role of exercise intensity under both matched and unmatched energy conditions.

Previous studies have consistently suggested that exercise volume is a major determinant of hepatic fat reduction in individuals with MASLD (6, 9, 24). However, emerging evidence indicates that the beneficial effects of exercise on hepatic steatosis cannot be fully explained by volume or energy deficit alone, highlighting the potential importance of exercise intensity as an independent factor (7, 27, 28). Impey et al. proposed the “muscle glycogen threshold hypothesis,” which suggests that when skeletal muscle glycogen is reduced to a critical level—through diet or exercise—it triggers greater metabolic adaptations, including enhanced fatty acid oxidation (15). Because higher-intensity exercise accelerates glycogen depletion (29), it may induce these adaptations more efficiently, thereby amplifying metabolic benefits. Furthermore, reduced glycogen availability may facilitate postprandial non-oxidative glucose disposal, a key element in improving metabolic flexibility (16). These mechanistic insights provide a plausible explanation for why the effect of exercise-induced HFC reduction is partially independent of weight loss (7, 27, 30). Nevertheless, research directly comparing the differential effects of exercise modalities on hepatic fat reduction remains limited (8). The only trial that adequately controlled energy expenditure between moderate- and high-intensity exercise was underpowered due to a small sample size, making it difficult to draw firm conclusions regarding their relative efficacy (10).

It is crucial to clarify that our study does not negate the established impact of exercise volume on hepatic fat reduction. AMP-activated protein kinase, a widely accepted therapeutic target for exercise in MASLD, functions through a complex cascade integrating energy expenditure signals, upstream kinases, and downstream metabolic pathways (12). Consequently, its activation is influenced not only by short-duration high intensity but also by total exercise volume, the effect of which will be investigated by the AMPED study (31).

The distinct advantage of high-intensity intervention lies in its potential to achieve HFC reductions comparable to MICT with reduced time and energy expenditure, or potentially superior reductions when energy is matched. This provides diverse, efficient intervention options for the heterogeneous MASLD population. However, the optimal physiological boundaries for intensity and volume in this population remain undefined. It cannot be assumed *a priori* that the high-volume HIIT (400 kcal) will inherently outperform low-volume LHIIT (200 kcal). Individuals with metabolic dysfunction may exhibit impaired metabolic flexibility or maladaptation to high physiological loads (32, 33). Therefore, determining the effective physiological threshold and establishing safe dosage boundaries based on individual metabolic characteristics represent critical questions worthy of further investigation.

Collectively, the results of this study facilitate a flexible approach to exercise prescription for MASLD, tailoring the regimen to the time availability and fitness level of MASLD population. We propose that low-volume HIIT is an optimal strategy for time-poor individuals, while high-volume HIIT serves those prioritizing maximal fat reduction. For patients unable to tolerate high intensities, volume-compensated moderate-intensity exercise offers a dependable alternative for managing HFC.

